| Item 12. How well (actual)?: If intervention adherence or fidelity was assessed, describe the extent to which the intervention was delivered as planned                                    | Not applicable for protocol                                                                                                                                                                                                                                                                                                                                                                                                                                                | Not applicable for protocol                                                                                                                                                                                                                                                                                                                                                                                                                                                |

approach being used in this study [21]. Patients who meet one of these criteria will be permitted to see a weekend allied health staff member despite them being on a ward during a ‘control’ period. Local nursing or medical staff will identify if the patient meets the pre-determined set of criteria, which allows for them to be seen by an allied health professional over a weekend. This will be escalated to the site allied health director or project site liaison who will approve provision of the service following a final check against the ‘clinical exception’ criteria. These criteria will be suggested by ward-

level staff during pre-trial group interviews, and managers through key-informant and group interviews and will vary from site to site. Staff will be asked to provide evidence to support their request for a clinical exception criteria (for example, research papers, local incident reports, hospital policy), and project investigators will determine whether the strength of evidence presented warrants formation of a clinical exception criterion. The frequency of clinical exceptions under each criterion will be recorded to monitor control condition fidelity. Project data collectors at each site will be present on

[figure not shown]

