### **Procedure**

Approval to conduct this study has been obtained from the Monash Health Human Research Ethics Committee (EC00383 - representing Dandenong Hospital) and the Melbourne Health Human Research Ethics Committee (2013.283 - representing Western Hospital (Footscray)) and this trial has been registered with the Australian New Zealand Clinical Trials Registry (ACTRN12613001231730 (study 1) and ACTRN12613001361796 (study 2)). It is anticipated that data collection will commence in February 2014 and be completed in June 2015 with reports and publications finalised by June 2016. A multi-site project executive committee has been developed consisting of all project investigators. This executive committee has developed a project communications plan in consultation with representatives from the Victorian Government, Department of Health. Further pre-trial communications with relevant health services unions, local site clinicians, managers and executives will also be undertaken prior to trial commencement. Extensive staff engagement has been undertaken for this project at both study sites prior to trial commencement.

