### **Trial safety**

The process of disinvestment in allied health services has the potential to be detrimental to patient safety and/or organisational outcomes. The checking of stopping rules and development of clinical exceptions will, therefore, be used to ensure safety. A stopping rule allows data to be monitored and the trial to be stopped if there is evidence of a lack of safety or efficacy associated with the intervention [34]. During study 1, interim analyses will be conducted monthly to ensure that patient outcomes have not dropped below a pre-specified non-inferiority margin. This margin represents the maximum amount of gain anticipated if the amount of resources being saved were to be reallocated to another purpose. Discussion groups with clinicians and project investigators initially determined that the non-inferiority margin should be 0.8 multiplied by the standard deviation of the targeted outcome. This is equivalent to 'Cohen's large effect size' [35]. However, review of the standard deviations for the outcomes that these stopping rules would be applied to revealed that these margins were too wide to be acceptable to the management of participating hospitals. As a result of these consultations, the following stopping rules were developed:

1. The 95% CI of the effect (difference between means) of having no weekend allied health services exceeding a 1-day increase in mean length of stay.
2. The 95% CI of the effect (difference between proportions) of having no weekend allied health services exceeding an absolute change of 0.02 (2%) in the outcomes of the proportion of patients who stay longer than their average inlier Australian Refined Diagnosis-Related Group (ARD-RG), the proportion of patients who experience one or more of the previously specified adverse events, or the proportion of patients who are unexpectedly readmitted within 28 days.

Management at each site also reserved the right to review other study data (for example, the proportion of patients discharged on the weekend) in determining whether the study should continue at each site. Interim analysis will be conducted during each month of study 1 and reported back to the project executive committee.

The project executive committee will then forward their recommendations along with blinded data to an independent data-monitoring committee at each site to make a determination as to whether the project should be ceased on the basis of the analysis conducted.

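### Interim analyses go first to a committee of all investigators, which passes its own recommendation and undefined 'blinded' data to the independent monitoring committees

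*Protocol*

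**What the plan says.** Three places in the protocol fix the procedure.

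- **Trial safety**, on who sees the results first: "Interim analysis will be conducted during each month of study 1 and reported back to the project executive committee".
- **Procedure**, on who sits on that body: "A multi-site project executive committee has been developed consisting of all project investigators".
- **Trial safety**, on what happens next: the executive committee is to "forward their recommendations along with blinded data to an independent data-monitoring committee at each site". The task of the independent committees is "to make a determination as to whether the project should be ceased on the basis of the analysis conducted".

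The stopping rules in the same section are written as the effect of withdrawing the service. The first concerns "having no weekend allied health services exceeding a 1-day increase in mean length of stay". The second applies a 0.02 absolute margin to three proportions, also as the effect of having no service.

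The Masking section describes mock codes that hide ward identity and time sequence from the statistician of the final analysis. It states no masking for whoever prepares the interim analyses or for the executive committee. The Trial safety section does not say what *blinded* means for the data passed on.

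**The concern.** An independent monitoring committee exists so that the decision on harm is taken by people with no stake in the trial, on evidence that reaches them unfiltered. Here the order is reversed. The investigators receive the analysis, form a view and send that view on with the data. The independent committees act second, with the investigators' recommendation already in front of them.

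Two things are at stake. The first is the independence of the safety decision, in a trial whose own text accepts that withdrawing services could harm patients. The second is the confidentiality of accumulating results: everyone who conducts the trial is on the committee that receives them each month. The undefined word *blinded* adds to this, because the rules can be applied as written only by someone who knows which condition is which.

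**Working it through.** No stated figure is in dispute. The check is mainly a comparison of sections, with one piece of arithmetic on whether masking the condition could work.

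**1. Routing.** Trial safety names the executive committee as the body to which the monthly analysis is reported. Procedure says that body consists of all project investigators. Trial safety then has it forward two things: its recommendations and blinded data. Both links are stated, not inferred.

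**2. Masking.** The Masking section covers the final-analysis statistician. Nothing there extends to the interim stage.

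**3. What *blinded* could mean.** Three readings are open:
- de-identified at patient level (the text after the stopping rules says data are de-identified once linkage is done);
- coded by ward (elsewhere the protocol uses the word for ward identity and order);
- coded by condition.

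Only the third interferes with the stopping rules.

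**4. Would coding by condition conceal anything?** Inputs: 6 wards per site, 7 months of study 1 and 174 admissions per ward per month (Group 1), with one ward withdrawn each month (Abstract). Check against the protocol's own total: 174 × 6 × 7 = 7,308, which agrees.

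All wards have the service in month 1 and none in month 7, so m − 1 wards are without it in month m. Cumulative ward-months after month m are:
- no service: m(m − 1)/2
- service: 6m − m(m − 1)/2

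Multiplying by 174 gives expected admissions per site:

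| After month | Ward-months, service : none | Admissions, service : none |
|---|---|---|
| 1 | 6 : 0 | 1,044 : 0 |
| 2 | 11 : 1 | 1,914 : 174 |
| 3 | 15 : 3 | 2,610 : 522 |
| 4 | 18 : 6 | 3,132 : 1,044 |
| 5 | 20 : 10 | 3,480 : 1,740 |
| 6 | 21 : 15 | 3,654 : 2,610 |
| 7 | 21 : 21 | 3,654 : 3,654 |

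Month 1 has no comparison. Months 2 to 7 give six comparative looks per site, 12 over two sites. In months 2 to 6 the groups differ in size, so anyone who knows the design can tell which code is which. Only at month 7 are they equal.

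**5. Reading the steps together.** If *blinded* means condition-masked, it hides little and still prevents a report that states the rules' own quantity, the effect of no service. If it means something weaker, the routing in step 1 is unaffected.

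**The case against.** The strongest reply is that much of the possible harm is not in the text. Four stronger readings are tempting, and the protocol does not support them.

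- *Masking is the wrong way round: investigators unmasked, independent committees masked.* The protocol never says that the executive committee sees results by condition, nor that condition is hidden from the independent committees. Both would be inferences.
- *The independent committees cannot judge harm.* They are to decide on the basis of the analysis conducted, which suggests that they see it. The table also shows that codes for condition would be readable at every comparative look before the last.
- *Interim results would change the clinical exception criteria.* It is true that "project investigators will determine whether the strength of evidence presented warrants formation of a clinical exception criterion". But the Study 1 control condition section describes a pre-determined set, suggested in pre-trial interviews, and states no revision after an interim look. Individual requests are approved by the site allied health director or project site liaison, and ongoing ward communication about the criteria is given to data collectors.
- *The study 2 model is biased by knowledge of study 1.* The protocol intends study 2 to learn from study 1: stakeholders examine its incident and exception data, and allied health managers propose and select the model.

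It can also be said that ward allocation is open, so investigators cannot be masked to condition. That is correct, but it does not prevent withholding accumulating comparative results from them.

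These replies remove the claims about outcome. They do not touch the sequence: investigators first, then a recommendation, then the independent decision.

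**Conclusion.** The point holds as one of independence and confidentiality in the monitoring procedure. The protocol states that procedure, so this is not detail left for a later document. Each month of study 1, a body made up of all investigators receives the interim analysis before the independent committees do, and its recommendation goes with the data to them. That happens at six comparative looks per site, 12 in all. This count measures exposure. No size of bias can be derived from the protocol, and none is claimed.

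The second part is an undefined term. It obstructs the stopping rules only if *blinded* means condition-masked, and in that case the masking gains little.

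The table assumes cumulative analyses, the planned average throughput and no exclusions. If each look used that month's data alone, the ward split in months 2 to 6 would be 5:1, 4:2, 3:3, 2:4 and 1:5. It would be equal at month 4, and month 7 would offer no comparison. The routing point depends on none of these assumptions.

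This should be changed, but it does not invalidate the design.

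**What to change.** Rewrite the reporting paragraph in Trial safety so that:

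1. whoever prepares the interim analysis sends the comparative report, with conditions identified, directly to the independent committees;
2. those committees return only their recommendation to the executive committee, which sees no comparative results until study 1 is complete at both sites;
3. the term *blinded data* is replaced by a statement of what is concealed and from whom.

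The stopping thresholds and the monthly schedule are unchanged.

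Costs: the executive committee loses its monthly view of comparative results. The protocol does not name the interim analyst; if that person sits on the executive committee, the results must be kept confidential from the other members. The sites start in February and April 2014, so seven months of study 1 run to August and October. The committee would therefore wait about two months after the first site finishes. The new text should make clear that this does not block the planned use of study 1 incident and exception data in developing the study 2 model. It should also say how the right of site management to review other study data fits the new route.

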### Recruitment

A waiver of consent was requested and granted for researchers to access routinely collected, hospital administrative data (for example, length of stay, hospital readmission) covering these forms of data for participants in Group 1. Written consent will be obtained from all participants (where the waiver of consent does not apply). Written consent will be obtained from participants in Group 2 by a project team member (MS, MG) or research assistant. They will be identified as being potentially eligible for consent to participate by screening of ward handover sheets and communication with ward staff. Written consent will be obtained from participants in Group 3 by a project team member (ES, SP, LS, DM, LOB). They will be notified of the possibility of participating in this project by Email and verbal communication.

### Data analysis

#### Sample size estimation

The sample size in this study is governed by the patient throughput on the participating wards over the trial

period. Non-inferiority trials do not preclude testing of superiority and can be done so without statistical penalty [36]; hence, we undertook power calculations for studies 1 and 2 from a superiority analysis perspective. Current data from study wards indicates there will be 7,308 patient admissions in total per study per site. We used the approach for conducting power analyses for stepped wedge trials advocated by Hussey and Hughes [37] based upon the Wald statistic. We applied this approach to 3 of our primary outcomes and demonstrated > 90% power in each case for study 1 and study 2 (Table 3). We reiterate that the actual sample size to be used in the trial has been determined primarily by practical considerations, particularly the availability of suitable wards at the participating sites.

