#### **Group 1**

'All patients on participating wards.' This group will consist of patients admitted to acute medical or surgical wards involved in the trial who are over the age of 18 years. Paediatric patients will be excluded from this study as they are not routinely seen on the selected wards (none are paediatric units or have paediatric beds) and have different provisions for service delivery. It is anticipated, based on previous patient flow data, that each ward will have an average of 174 patient admissions per month during the trial. This means that 6 wards at 1 site will have 7,308 patient admissions during the 7 months of study 1 and 7,308 during the 7 months of study 2. This will lead to an anticipated total of 29,232 patient admissions during the overall study period.

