### Statistical analysis

**Study 1** Both non-inferiority and superiority analyses will be conducted. For non-inferiority analyses, if the non-inferiority null hypothesis is to be rejected, the upper limit of the CI around the observed difference should be less than the non-inferiority margin. Multi-level, mixed-effects generalised linear model analyses will be used to construct the 95% CIs that compare effectiveness and safety outcomes between groups. These models will nest patient admissions within wards, treating both as random factors, to account for the clustered nature of these data. Weekend allied health service delivery model provided will be treated as a fixed factor. The distribution of the length of stay outcome will be examined ( $\pm$  transformations as indicated) as a part of model building as these data are commonly skewed. Data from

**Table 3 Outcome of power analysis for three outcomes for each study at each site (assuming six wards per site), and for both sites combined**

| Outcome                                                                                | Proportion 1
(weekend allied
health services) a | Proportion 2
(no weekend allied
health services) | Single site
or both
sites combined | Assumed
coefficient
of variation | Assumed
number of
patients per
study | Power |
|----------------------------------------------------------------------------------------|------------------------------------------------------------------|--------------------------------------------------------|------------------------------------------|----------------------------------------|-----------------------------------------------|-------|
| Proportion of patients who stay longer than their AR-DRG average inlier length of stay | 0.40                                                             | 0.42                                                   | Single                                   | 0.4                                    | n = 7,000 b                        | 0.65  |
| Proportion of patients who are readmitted within 28 days                               | 0.10                                                             | 0.12                                                   | Single                                   | 0.4                                    | n = 7,000 b                        | 0.96  |

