| Proportion of patients who experience at least one of the adverse events listed        | 0.10                                                             | 0.12                                                   | Single                                   | 0.4                                    | n = 7,000 b                        | 0.96  |
| Proportion of patients who stay longer than their AR-DRG average inlier length of stay | 0.40                                                             | 0.42                                                   | Both                                     | 0.4                                    | n = 14,000 b                       | 0.99  |
| Proportion of patients who are readmitted within 28 days                               | 0.10                                                             | 0.12                                                   | Both                                     | 0.4                                    | n = 14,000 b                       | >0.99 |
| Proportion of patients who experience at least one of the adverse events listed        | 0.10                                                             | 0.12                                                   | Both                                     | 0.4                                    | n = 14,000 b                       | >0.99 |

AR-DRG, Australian Refined Diagnosis-Related Group.

aBaseline proportions based on data drawn from administrative datasets at participating sites covering a 12-month period.

bNote that for the single site analyses we assume there will be 7,308 per study, but use only 7,000 in the power analysis to allow for loss of patients during the transition phases between intervention and control conditions and for transfers between study wards. Correspondingly, we use 14,000 when considering the power of both sites combined.

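### All six power values in Table 3, and the text's claim of more than 90% power, are too high for the stated design: about 0.16 to 0.33 per site and 0.27 to 0.58 combined

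*Protocol*

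**What the plan says.** Under Group 1, the protocol expects that "each ward will have an average of 174 patient admissions per month during the trial", and that "6 wards at 1 site will have 7,308 patient admissions during the 7 months of study 1". Footnote b of Table 3 lowers this figure: the authors "use only 7,000 in the power analysis to allow for loss of patients during the transition phases" and for transfers between wards. They use 14,000 for the two sites together.

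Under Sample size estimation the method is named: "We used the approach for conducting power analyses for stepped wedge trials advocated by Hussey and Hughes [37] based upon the Wald statistic". The section concludes that this "demonstrated > 90% power in each case for study 1 and study 2 (Table 3").

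Table 3 is titled "Outcome of power analysis for three outcomes for each study at each site (assuming six wards per site), and for both sites combined". Its assumed CV is 0.4 throughout, and it prints:

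| Outcome | Proportions | One site, n = 7,000 | Both sites, n = 14,000 |
|---|---|---|---|
| Stay beyond the AR-DRG average | 0.40 vs 0.42 | 0.65 | 0.99 |
| Readmission within 28 days | 0.10 vs 0.12 | 0.96 | >0.99 |
| At least one adverse event | 0.10 vs 0.12 | 0.96 | >0.99 |

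**The concern.** Two things look wrong. First, the sentence in the text promises more than 90% power in every case, while the table beneath it prints 0.65 for the AR-DRG outcome at one site. Second, values of 0.96 and above for a two-point difference are implausibly high for six wards and 7,000 patients once ward and month effects are in the model.

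The protocol plans site-level analyses as well as patient-level analyses across sites. For study 1 it requires the upper confidence limit to lie below the non-inferiority margin. Trial safety sets a limit of 0.02 for the proportion outcomes. If the real precision is much poorer than Table 3 implies, a non-significant or inconclusive result on these outcomes could be given a weight that the design does not support.

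**Working it through.** **Inputs.** Six wards and seven monthly periods per site, with one ward crossing over per step; 12 wards and two crossings per step for both sites. Patients per ward-month: 7,000 / (6 × 7) = 166.7, and 14,000 / (12 × 7) = 166.7. As a check, 174 × 6 × 7 = 7,308. CV is 0.4; proportions are as tabled.

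**Assumptions not stated in the protocol.** Two-sided 5%, inferred from the models that "will be used to construct the 95% CIs that compare effectiveness and safety outcomes between groups". The CV is taken as the between-ward SD divided by the mean proportion p̄. Using the baseline proportion instead moves the results only in the third decimal.

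**Formula.** With I wards, T periods, s² = p̄(1 − p̄)/n per ward-period and t = 0.4p̄:

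Var = I·s²(s² + T·t²) / [(I·U − W)s² + (U² + I·T·U − T·W − I·V)t²], and power = Φ(0.02/SE − 1.96).

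For 6 × 7, U = 21 and W = V = 91. The bracket is therefore 35s² + 140t². Withdrawal and roll-out layouts give the same variance.

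**One site, n = 166.7.**
- 0.40 vs 0.42: s² = 0.2419/166.7 = 0.001451; t² = 0.164² = 0.0269; SE = 0.0208; power = Φ(0.961 − 1.96) = 0.16.
- 0.10 vs 0.12: s² = 0.0979/166.7 = 0.000587; t² = 0.044² = 0.00194; SE = 0.0131; power = Φ(1.530 − 1.96) = 0.33.

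**Both sites.** Doubling the wards halves the variance. SE = 0.0147 and 0.0092; power = 0.27 and 0.58.

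**Trying to reproduce Table 3.**
- With n = 1,000 per ward-month (7,000/7, not divided by six wards), one site gives 0.651 and 0.959. These match 0.65 and 0.96.
- With n = 1,000 on 12 wards × 7 months, the result is 0.913 and 0.9995. The second fits >0.99; the first does not fit 0.99.
- The combined AR-DRG value needs about 1,670 per ward-month to reach 0.99. With 14,000/7 = 2,000 it is 0.997.

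**Variants at the stated patient numbers** (0.40 vs 0.42 / 0.10 vs 0.12):

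| Variant | One site | Both sites |
|---|---|---|
| Printed in Table 3 | 0.65 / 0.96 | 0.99 / >0.99 |
| Two-sided 5%, CV 0.4 | 0.16 / 0.33 | 0.27 / 0.58 |
| One-sided 5%, CV 0.4 | 0.25 / 0.46 | 0.39 / 0.70 |
| Two-sided, CV 0 | 0.24 / 0.51 | 0.43 / 0.81 |
| CV 0.4, no time effects | 0.32 / 0.65 | 0.56 / 0.91 |
| No clustering, no time effects | 0.40 / 0.76 | 0.67 / 0.97 |
| Same, one-sided 5% | 0.52 / 0.85 | 0.78 / 0.98 |

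The unclustered rows use SE = √{[p₁(1 − p₁) + p₂(1 − p₂)]/(N/2)}. For 0.40 vs 0.42 and N = 7,000 this is √(0.4836/3,500) = 0.01175, giving Φ(1.702 − 1.96) = 0.40. Ward and month terms can only enlarge this SE, so these rows are a ceiling. Every printed value lies above it.

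**Precision against the 2-point margin.** Expected 95% half-widths are 1.96 × SE. Per site they are about 4.1 points (AR-DRG) and 2.5 points (readmission, adverse events). Combined they are about 2.9 and 1.8 points. With no true difference and the baseline proportions, the power to show non-inferiority is about 0.16 and 0.36 per site, and 0.28 and 0.62 combined.

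**Study 2 at the five-ward site.** Five wards over six months (U = 15, W = V = 55, n = 166.7) give SE = 0.0249 and 0.0156, and power of about 0.12 and 0.25.

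**The case against.** The strongest reply is that the sample size was never derived from this calculation. The protocol says that it was governed by patient throughput and the availability of suitable wards. That stands, and it means the error did not set enrolment. It does not make the printed figures right, and the protocol offers them as evidence of adequacy.

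The sentence about more than 90% power can also be read as referring to the two-site rows only, which are all printed above 0.90. The wording is loose enough to allow this, so the clash with 0.65 is the lesser part of the point. The two-site values are themselves unattainable.

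It is fair to say that alpha, sidedness and the scale of the CV are not stated. The recomputed values therefore depend on assumptions and are best shown as a range. Scaling the CV to the effect gives about 0.23 / 0.44 and 0.40 / 0.72. No variant tried recovers the table.

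A reader might infer three stronger things that the document does not support:
- That one slip, 1,000 patients per ward-month, explains the whole table. It matches the three single-site rows and is compatible with the two >0.99 rows, but not with the combined AR-DRG row. The cause is likely but inferred.
- That study 1 as a whole will be inconclusive. The check covers only the proportions in Table 3. Mean length of stay, with its own 1-day limit, is not in the table, and the adverse-event primary outcome is defined as a rate per person-time.
- That the analysis across both sites rescues the inference. For the AR-DRG outcome its half-width is still about 2.9 points, and its non-inferiority power about 0.28.

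**Conclusion.** The point holds. None of the six values in Table 3 follows from the stated design, and the claim of more than 90% power is unsupported. On the protocol's own method and inputs, with two-sided 5% and the CV applied to the proportion, power is about 0.16 and 0.33 per site and 0.27 and 0.58 combined. The conclusion that every printed value is too high does not rest on those assumptions or on any account of how the error arose, because the unclustered ceiling is also exceeded in every row.

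The practical effect is confined to the proportion outcomes. At site level the expected interval is wider than the margin for all three. Combined, this remains so for the AR-DRG outcome, while the interval for readmission and adverse events falls slightly inside the margin. The five-ward site in study 2 is weaker still.

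**What to change.** 1. Recompute Table 3 at about 167 patients per ward-month and replace all six values. State alpha, sidedness and what the CV scales.
2. Remove the claim of more than 90% power from Sample size estimation.
3. Add the study 2 case with five wards at one site (about 0.12 and 0.25 there over six months) and the matching two-site row with 11 wards.
4. Report the expected 95% half-widths for the proportion outcomes, per site and combined, beside the 2-point margin, with the non-inferiority power when there is no true difference.
5. State that for these proportion outcomes a non-significant or inconclusive result is not evidence of no effect, at site level and, for the AR-DRG outcome, also combined. Do not add a statement that the two-site analysis carries the inference.

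The cost is one recalculated table and a few sentences, and stated figures that are much less favourable. Enrolment, wards and schedule do not change.
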